#### Phase 3 (initial implementation): NOM-implementation in selected hospitals

NOM for selected frail older adults will be implemented in 14 selected hospitals (figure 2, collaborators listed in online supplemental materials 1). Based on the experience of these hospitals, the NOM implementation protocol and/or the educational material will be optimised. To safeguard implementation of NOM in the long term, the NOM protocol pays explicit attention to the involvement of all relevant healthcare providers by informing those involved before, during and after implementation, and by collecting data on relevant feasibility parameters as described in the Bowen model.^25^ To achieve this, the site principal investigator will be asked to establish a local project team. The team should represent all groups involved in NOM, including relevant physicians and, as applicable, residents of the involved departments, specialised nurses, physician assistants and hospital management. Prior to implementation, this local team will meet with the researchers for an interview to train them in applying the SDM and the NOM implementation protocol, and to collect details on their specific needs for the implementation.

10.1136/bmjopen-2023-083429.supp1Supplementary data

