#### Phase 4 (nationwide implementation): NOM-implementation in all hospitals in the Netherlands and project analysis

Phase 4 is an expansion of phase 3 to reach nationwide implementation. The implementation strategy will essentially be the same as in phase 3. Due to the increase in number of hospitals, the supervision and contact with the researchers and steering committee will be less intensive than in phase 3. In practice, this means that the NOM protocol will be implemented, but the interviews with healthcare professionals in the hospitals (prior to start and 6 months after start) will be omitted. To ensure that all information on SDM and NOM implementation is available continuously to both patients and healthcare providers, a dedicated website will be developed and maintained. To effectively reach a broad audience of healthcare providers and keep them updated on the implementation process and learning experiences, our goal is to give presentations at the annual meetings of orthogeriatric scientific associations, as well as associations for general practitioners and elderly care physicians (table 3). In addition, time slots for presentations will be requested at the meetings of the regional trauma networks. Ultimately, we aim to include SDM on NOM or operative treatment for proximal femoral fractures in select frail older adults in the National guidelines for hip fracture treatment and operative care in older adults.

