### Outcome measures and data collection

The primary outcome measure (for phases 3 and 4) is (change in) the NOM rate. Type of treatment (NOM vs operative treatment) will be extracted from the DHFA. The DHFA is a national database, including over 95% of Hip fracture patients and can provide automated anonymous patient data up to 1 year after hip fracture treatment. To evaluate the effect of the implementation, the change in NOM rate and operative rate for the targeted population will be evaluated and compared with the rate prior to implementation. This will be calculated using the annual national DHFA data from the 2 years preceding implementation per hospital, as baseline. The postimplementation NOM rate will be collected immediately after completion of phase 4, as well as at the end of 2025. The secondary outcome measures (for phase 3 only) will be collected during semistructured interviews with patients/proxy or next-of-kin, 4–6 weeks after inclusion. These are the satisfaction with the chosen treatment on a numeric rating scale (0–10), their valuation of the information received during the SDM process, and if the patient’s needs were respected enough in the treatment decision. The interview sheets (in Dutch), used for patient or healthcare provider interviews in phases 1–3, are included in online supplemental materials 2.

10.1136/bmjopen-2023-083429.supp2Supplementary data

The following patient data will be also collected in phases 3 and 4 from the DHFA at 3 months and 1 year after hip fracture treatment (emerging from the patients’ medical records). Patient characteristics (age, sex, ASA, FAC), prefracture situation (residence, mobility, Katz Activities of Daily Living (ADL) score), fracture details (fracture classification, affected side), hospital details (hospital length of stay and intensive care length of stay) and outcome details (complications, revision surgeries, readmission, 30-day mortality and time until death).

Data will be collected for each patient who meets the eligibility criteria. To reduce the administrative burden, the DHFA database will be used as much as possible. Data from the DHFA will be imported in a Castor EDC database, in which hospitals can only see their own data. The datasets of all hospitals will be combined for the final analysis.

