### Statistical analysis

Data will be analysed by using the SPSS V.28 or higher (SPSS). Normality of continuous data will be tested with the Shapiro-Wilk test, and homogeneity of variances will be tested using the Levene’s test. A p<0.05 will be taken as threshold of statistical significance. Missing values will not be imputed.

The primary outcome, NOM rate, will be determined by dividing the number of patients treated with NOM by the total eligible number of patients (per participating centre and for all participating centres combined).

All continuous data will be reported as mean with standard deviation (SD; if normally distributed based on Shapiro-Wilk test) or as median with quartiles (if not normally distributed). Categorical data will be reported as number with percentage. Preimplementation and postimplementation data will be compared with a Student’s t-test (continuous data, normally distributed), Mann-Whitney U-test (continuous data, non-normally distributed), or a χ^2^ or Fisher’s exact test (categorical data), as applicable. The analysis will be stratified by NOM versus operative treatment, and further stratified as feasible depending on the final study population, for example, by time since NOM implementation, prefracture mobility, ADL status, fracture classification or bilateral fracture.

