### Project timeline

Phase 1 of the study started in June 2023 and ended in August 2023. Phase 2 started in June 2023 and ended in October 2023. Phase 3 started in September 2023 and will approximately end in October 2024. Phase 4 will start in June 2024 and will approximately be concluded in June 2025.

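### The combined pre/post comparison of the NOM rate is not stratified by hospital, although hospitals start at different times and the post rate is read on common dates, so a change in hospital mix can look like a change in practice

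*Protocol article*

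**What the plan says.** All places are in the Protocol article, Methods and analysis.

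- **Baseline** (Outcome measures and data collection): "using the annual national DHFA data from the 2 years preceding implementation per hospital, as baseline". Each hospital contributes the same length of time, counted back from its own start.
- **Post-implementation** (same section): "The postimplementation NOM rate will be collected immediately after completion of phase 4, as well as at the end of 2025". These are two common calendar dates. The section states neither when a hospital's post period begins nor how long it lasts.
- **Starts** (Project timeline): phase 3 runs from September 2023 to about October 2024. For the later hospitals the section says: "Phase 4 will start in June 2024 and will approximately be concluded in June 2025".
- **Early hospitals** (Phase 3): the protocol "will be implemented in 14 selected hospitals". The Phase 4 section says that later hospitals get less intensive supervision.
- **Estimator** (Statistical analysis): NOM patients divided by eligible patients, "per participating centre and for all participating centres combined". Categorical data before and after are compared with a chi-square or Fisher's exact test. Stratification by time since implementation is named as an example, if feasible. No stratification or weighting by hospital is stated for the combined comparison.

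**The concern.** With an equal baseline for all hospitals and post periods that run from staggered starts to a common end, early hospitals supply a larger share of patients after implementation than before. A crude combined rate then compares two different mixes of hospitals. If early and late hospitals have different underlying NOM rates, part or all of the combined change is a change in mix, and an unadjusted test cannot separate the two.

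The change in NOM rate is the primary outcome for phases 3 and 4, and the Future perspective section expects the project's products to feed guideline updates. A shift of a few points from hospital mix could be reported as an effect of implementation, or could hide one.

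**Working it through.** **1. The plan's own figure.** The Sample size calculation section gives 17 225 patients aged 70 or older, of whom about 25% live in an institution: 0.25 × 17 225 = 4306, which agrees with its figure of about 4300. About half meet the criteria, so about 2150 eligible patients a year. Two baseline years give n₀ = 2 × 2150 = 4300.

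**2. Follow-up from the stated dates.** A phase 3 hospital starting in September 2023 has about 21 months at June 2025 and 27 at the end of 2025; these are maxima. A phase 4 hospital has 0 to 12 and about 6 to 18 months. With starts spread evenly (assumption) the means are 6 and 12.

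**3. Share of patients from phase 3 hospitals.** Let s be their baseline share (assumed 20%, range 15 to 30%) and m the months of follow-up:

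s₁ = s·m_early / [s·m_early + (1 − s)·m_late]

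- June 2025: 0.20 × 21 / (0.20 × 21 + 0.80 × 6) = 4.2/9.0 = 46.7% (38% to 60% over the range of s).
- End of 2025: 0.20 × 27 / (0.20 × 27 + 0.80 × 12) = 5.4/15.0 = 36.0%.

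**4. Spurious change when every hospital keeps its own rate.** Shift = (s₁ − s) × (p_early − p_late). The NOM rates are assumptions. Rows use s = 20%; the last column is the chance of p<0.05 (two-sided, pooled-variance z test, equivalent to chi-square).

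| Reading and months (early v late) | NOM rate, early v late | Combined rate, pre → post | Shift (points) | Chance of p<0.05 |
|---|---|---|---|---|
| June 2025, 21 v 6 | 20% v 20% | 20.0% → 20.0% | 0 | 5% |
| June 2025, 21 v 6 | 25% v 20% | 21.0% → 22.3% | +1.3 | 20% |
| June 2025, 21 v 6 | 30% v 20% | 22.0% → 24.7% | +2.7 | 59% |
| June 2025, 21 v 6 | 40% v 20% | 24.0% → 29.3% | +5.3 | 99% |
| June 2025, 21 v 6 | 20% v 30% | 28.0% → 25.3% | −2.7 | 54% |
| June 2025, phase 3 starts spread, 14.5 v 6 | 30% v 20% | 22.0% → 23.8% | +1.8 | 28% |
| June 2025, all phase 4 starting June 2024, 21 v 12 | 30% v 20% | 22.0% → 23.0% | +1.0 | 17% |
| End of 2025, 27 v 12 | 30% v 20% | 22.0% → 23.6% | +1.6 | 34% |
| End of 2025, 27 v 18 | 30% v 20% | 22.0% → 22.7% | +0.7 | 12% |

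Reversing the 40% v 20% row gives (0.467 − 0.20) × (20 − 40) = −5.3 points. At s = 30% that contrast gives (0.60 − 0.30) × 20 = 6.0 points.

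**5. The same data, stratified.** The Mantel-Haenszel risk difference is Σw_h(p₁ₕ − p₀ₕ)/Σw_h with w_h = n₀ₕn₁ₕ/(n₀ₕ + n₁ₕ). If no hospital changes, every term is zero, so the result is 0.0 points in every row above. A post period of equal length for all hospitals also gives 0.0.

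**6. Size of the per-centre rates.** If there are 75 hospitals (assumption), 2150/75 is about 29 eligible patients per hospital-year. A hospital two months in has 29 × 2/12, or about 5.

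**The case against.** The strongest objection is that the post window is inferred. The text gives reading dates and does not say that each hospital contributes all its time since start. A common window, for example only the months after June 2025, would remove the shift. This stands as a condition on the finding. The inferred reading is still the natural one: the Outcome section collects data on every eligible patient in phases 3 and 4, and the Statistical analysis names time since implementation as a possible stratifier. No common window is fixed.

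Second, per-centre rates are planned and do not have the hospital-mix problem. That also stands, but at about 29 patients per hospital-year they cannot carry a national conclusion alone. Stratifying by time since implementation could help, but it is optional and is not stratification by hospital.

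Third, the size rests on assumed rates. True: with equal rates there is no shift. The Clinical impact section treats practice variation between hospitals as something to reduce, so equal rates cannot be presumed.

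A reader might infer more than the documents support:

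- *That the plan will show a false rise.* The early hospitals may have higher, equal or lower rates, so the direction is unknown.
- *That most phase 4 hospitals have under six months at June 2025.* With even starts it is about half (6/12, or 6/13 = 46% if June 2025 is counted in full). The six-month point in phase 3 is also a team interview about process, not a minimum exposure.
- *That phase 4 hospitals have no start date to anchor to.* Phase 4 says "the interviews with healthcare professionals in the hospitals (prior to start and 6 months after start) will be omitted", but this does not show that start dates go unrecorded, and a baseline set for each hospital presupposes one.

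**Conclusion.** The concern holds conditionally, and only for the combined comparison. The weight of the 14 phase 3 hospitals rises after implementation if post periods run from each hospital's start. The combined rate then shifts without any real change if early and late hospitals differ in NOM rate. With a 20% baseline share for the phase 3 hospitals, the shift at June 2025 runs from 0 with equal rates to about 5 points up or down with a 20-point contrast. With 30% v 20% it is 2.7 points at June 2025 and 1.6 at the end of 2025. The shares, rates and spread of starts are assumptions; the dates, the 14 hospitals and the eligible population come from the document. Since stratification removes the shift using data already collected, the plan should be changed.

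**What to change.** 1. In the Statistical analysis section, replace the crude combined pre/post rate and unadjusted test, for the primary comparison, with one stratified by hospital: a Mantel-Haenszel risk difference or a logistic model with hospital effects. Alternatively, standardise both periods to each hospital's baseline eligible count. Standardising is preferable if the aim is a national figure, because Mantel-Haenszel weights still lean towards hospitals with long follow-up when effects differ. Keep the per-centre rates.
2. In the Outcome section, state that each hospital's post period begins at its recorded start date. The reporting tool planned in phase 2 could hold that field.
3. Make the end-of-2025 reading the main one and the June 2025 reading interim, and report hospitals with short follow-up separately.

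The cost is slightly more analysis and a little less precision from small, late-starting hospitals. A reader might infer that the final extraction has to move into 2026 so that every hospital has a full year. It does not: stratification or standardisation removes the hospital-mix shift with the readings already planned, and a later extraction would sit badly with the two-year grant limit named under Strengths and limitations.

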### Sample size calculation

A formal sample size calculation was not made as the primary aim is implementation on a national level. To give an idea of the total national population size the following estimate was made: In 2020, 21 165 patients presented to a hospital in the Netherlands with a proximal femoral fracture.^26^ Of these 17 225 (81.5%) were aged 70 years or older. An approximate 25% of this population lived in a nursing home or other institution. Which projects to about 4300 patients as the primary target population of this study. Approximately half of these patients will meet our inclusion criteria and thus not all patients will be eligible for NOM, but this gives a broad estimate of the annual number of patients that should at least be considered for SDM on NOM and operative treatment.

### Statistical analysis

Data will be analysed by using the SPSS V.28 or higher (SPSS). Normality of continuous data will be tested with the Shapiro-Wilk test, and homogeneity of variances will be tested using the Levene’s test. A p<0.05 will be taken as threshold of statistical significance. Missing values will not be imputed.

The primary outcome, NOM rate, will be determined by dividing the number of patients treated with NOM by the total eligible number of patients (per participating centre and for all participating centres combined).

All continuous data will be reported as mean with standard deviation (SD; if normally distributed based on Shapiro-Wilk test) or as median with quartiles (if not normally distributed). Categorical data will be reported as number with percentage. Preimplementation and postimplementation data will be compared with a Student’s t-test (continuous data, normally distributed), Mann-Whitney U-test (continuous data, non-normally distributed), or a χ^2^ or Fisher’s exact test (categorical data), as applicable. The analysis will be stratified by NOM versus operative treatment, and further stratified as feasible depending on the final study population, for example, by time since NOM implementation, prefracture mobility, ADL status, fracture classification or bilateral fracture.

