### Strengths and limitations

The strength of this study is that it builds on an existing foundation of recent well-received (inter)national publications, countrywide initiatives involving SDM and advance care planning, and recent demands for assistance in the implementation of NOM from several hospitals. The project group includes experienced professionals from (orthopaedic) trauma surgery, geriatrics, epidemiology and implementation science from both university medical centres and general hospitals, supplemented with patient perspectives and experts in SDM and study methodology. A limitation of the project is the limited time period for the initial project. Achieving nationwide implementation within 2 years, which is the maximum allowed project duration of the grantor, might be an overoptimistic aim. However, the project will have developed a strong foundation on which future projects can build and will keep sharing its tools and information, even after completion. Another limitation is that the inclusion criteria might prove to be too narrow. There might be a larger group of patients for whom NOM could suit their preferences or goals of care. However, the project group has decided to keep strict criteria to prevent the pendulum swinging too far and causing undertreatment with long-term survival without functional recovery after opting for non-operative treatment, which results in potential decreased quality of life and associated adverse events. Depending on the results of the initial implementation, the inclusion criteria in the protocol might be adjusted to suit the needs of patients and healthcare providers. Finally, the NOM rate in the DHFA database might be an underestimation, as patients living in a nursing home might already have advance care plans preventing them from being transferred to the hospital in the case of a hip fracture. As the NOM implementation gains national traction more attention to advance care planning around hip fractures might lead to an unmeasured increase of the NOM rate in the prehospital setting. While reducing DHFA registration for this project, improved communication on patients wishes and integration of hip fractures in advance care planning, between patients and (geriatric) medical practitioners within and outside the hospital, is a desired effect that will improve the quality of NOM and patients’ treatment satisfaction.

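### The primary before-after NOM rate is tested without case-mix adjustment although case-mix items are collected, so a systematic shift in measured patient mix would be read as an implementation effect or would hide one

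*Protocol article*

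**What the plan says.** Outcome measures and data collection: "The primary outcome measure (for phases 3 and 4) is (change in) the NOM rate". The comparator is historical, calculated "using the annual national DHFA data from the 2 years preceding implementation per hospital, as baseline".

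Statistical analysis: the rate is "determined by dividing the number of patients treated with NOM by the total eligible number of patients", per centre and for all participating centres combined. "Preimplementation and postimplementation data will be compared with a" test chosen by data type. For a binary outcome that is a χ² test or a "Fisher’s exact test (categorical data), as applicable". "A p<0.05 will be taken as threshold of statistical significance". The section names no regression, standardisation or pooled stratified test.

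The same section stratifies the analysis by treatment (NOM or operation). Further strata are left to feasibility, with time since implementation, prefracture mobility, ADL status, fracture classification and bilateral fracture as examples.

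The items to be taken from the DHFA in phases 3 and 4 include "Patient characteristics (age, sex, ASA, FAC), prefracture situation (residence, mobility, Katz Activities of Daily Living (ADL) score") and fracture classification.

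Strengths and limitations warns that "patients living in a nursing home might already have advance care plans preventing them from being transferred to the hospital". It expects more advance care planning to reduce DHFA registration, and it allows the inclusion criteria to be adjusted after the initial implementation.

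**The concern.** The two periods contain different patients, with no randomisation and no concurrent control. Under Study population, one of three further criteria is enough for eligibility: malnutrition, FAC 2 or lower, or ASA 4–5. The denominator therefore mixes patients whose chance of choosing NOM plausibly differs. The article itself foresees two ways in which the people counted may change between periods.

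If the mix of eligible patients shifts systematically, the crude rate moves even when practice within each kind of patient stays the same. An opposite shift can cancel a real change. The primary result, which is meant to measure the effect of implementation, could then not separate changed practice from changed patients, although items that would help to do so are being collected.

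**Working it through.** **The plan's own figure.** Sample size calculation gives 17 225 patients aged 70 or older, of whom about 25% lived in an institution: 17 225 × 0.25 = 4306, stated as about 4300. About half meet the criteria, so about 2150 eligible patients a year. Two baseline years give about 4300.

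**Assumptions, not in the article.**
- One post-implementation year (about 2150 patients).
- A two-sided 5% level; the article does not state sidedness.
- Two kinds of eligible patient: ASA 4–5, with NOM rate a and a 40% share at baseline, and all others, with NOM rate b. Three pairs a/b are tried: 40%/15%, 30%/15% and 30%/20%.
- No change in practice, so a and b are the same in both periods.

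**Formulas.** With ASA 4–5 share s, the crude rate is s·a + (1 − s)·b. A shift Δs therefore changes it by Δs·(a − b). The probability of p<0.05 comes from the two-proportion z-test: pooled standard error for the critical value, unpooled for the distribution.

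**Example.** With 40%/15% and a share rising from 40% to 50%:
- before: 0.40 × 0.40 + 0.60 × 0.15 = 0.250
- after: 0.50 × 0.40 + 0.50 × 0.15 = 0.275
- pooled SE 0.01156, unpooled SE 0.01168
- Φ((0.025 − 1.96 × 0.01156)/0.01168) = Φ(0.20) = 0.58

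**Change in crude rate (percentage points) and probability of a significant result with no change in practice:**

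| Shift in ASA 4–5 share | Patients pre/post | 40%/15% | 30%/15% | 30%/20% |
|---|---|---|---|---|
| +10 points | 4300/2150 | +2.5; 57.9% | +1.5; 28.4% | +1.0; 14.4% |
| −10 points | 4300/2150 | −2.5; 60.0% | −1.5; 28.9% | −1.0; 14.3% |
| +5 points | 4300/2150 | +1.25; 19.4% | +0.75; 10.8% | +0.5; 7.3% |
| +2 points | 4300/2150 | +0.5; 7.3% | +0.3; 5.9% | +0.2; 5.4% |
| none | 4300/2150 | 0; 5% | 0; 5% | 0; 5% |
| +10 points | 2150/1075 | +2.5; 33.5% | +1.5; 16.7% | +1.0; 9.7% |

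**What a stratified test does.** A separate simulation (20,000 runs, 4300/2150 patients, baseline share 30%) compared the crude test with a Mantel-Haenszel test.
- No true effect, share rising from 30% to 40%: the crude test rejects in 15% (NOM 30%/20%), 53% (30%/10%) or 61% (40%/15%) of runs. The stratified test stays at about 5%.
- True common odds ratio 1.25, NOM 40%/15%: crude power is 92% with no shift, 58% if the share falls to 25% and 16% if it falls to 20%. Stratified power is 94%, 93% and 92%.

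The bias runs both ways, and it can be removed when the shifting characteristic is measured.

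**The case against.** The strongest reply concerns size. The article gives no shift. Eligibility narrows the room for one, since everyone is 70 or older, receives nursing-home-level care and meets a further criterion. The DHFA holds over 95% of hip fracture patients. All of this stands. With no shift the crude test is valid, and at 2 points the excess is negligible. National numbers are also a ceiling: the rate is defined over participating centres, and the article concedes that nationwide coverage in 2 years may be too optimistic.

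Adjustment has limits too. Patients kept out of hospital never enter the DHFA, so a model corrects only what shows in recorded items. Secular trend stays. Malnutrition is an eligibility criterion but is not in the listed data. The items are listed for phases 3 and 4, so their availability at baseline is not shown. These points limit what the fix can do; they do not argue against it.

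Two further replies are weaker. Optional stratification could expose some shifts, but its one fixed stratifier is the outcome itself, and the rest gives subgroup results rather than one adjusted change. Covariate models are often left to an analysis plan, but here the article names its tests, and none can adjust.

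A reader might infer that per-centre rates are biased by chance differences in mix. They are not: chance imbalance is already within the test's error rate, and only a systematic shift biases. A reader might also expect a clear gain in power. The article gives no basis for one, and the usual formula for covariate gain suits a continuous outcome in a randomised comparison, not this design.

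**Conclusion.** The point holds as a risk of unknown size, worth a cheap improvement. The primary comparison is fixed as crude and unadjusted between non-randomised periods, relevant covariates go unused, and the article itself anticipates changes in who is counted.

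Under the assumed NOM rates and full national numbers, false significance is about 14–60% for a 10-point shift in the ASA 4–5 share, 7–19% for 5 points and 5–7% for 2 points. With half the patients, a 10-point shift gives about 10–34%. Every figure rests on assumed NOM rates, shares and a one-year post window.

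A reader might conclude that the reported change will be wrong, that an error rate near 60% is to be expected, or that the crude test must be discarded. The article supports none of these: it reports no shift, 60% is the extreme of the range, and the crude test is valid if the mix is stable.

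**What to change.** In Statistical analysis, keep the crude NOM rates and the χ² or Fisher test, and add:

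- A prespecified logistic regression of NOM (yes/no) on period with a hospital term, adjusted for age, sex, ASA, FAC or prefracture mobility, residence, Katz ADL and fracture classification, as far as these are recorded in the 2 baseline years.
- One eligibility definition, applied identically in both periods.
- Pre- and post-implementation rates standardised to a common patient mix, and their difference with a 95% CI, beside the crude difference. The conclusion about implementation rests on both.
- Covariate missingness reported by period, and a complete-case analysis (the plan does not impute) with a sensitivity check. A category for unrecorded values should not carry the analysis: if recording differs by period, it becomes a proxy for period.
- A statement that adjustment does not remove secular trend, unmeasured prehospital selection or differences in malnutrition.

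Cost: an added paragraph, a regression in SPSS, which is already planned, and extraction of the same DHFA items for the baseline years. No new patients or visits are needed. The downside is that ASA or FAC scoring may respond to implementation, because both decide eligibility. Adjustment could then remove part of a real change; the crude result alongside makes that visible.

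### A Shapiro-Wilk p-value chooses summary and test for continuous data, so one variable can be handled differently across periods and strata; Levene's test has no stated use and only the equal-variance t-test is named

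*Protocol article*

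**What the plan says.** All of this is in the Statistical analysis section of the protocol article.

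- Preliminary tests: "Normality of continuous data will be tested with the Shapiro-Wilk test, and homogeneity of variances will be tested using the Levene’s test".
- Significance level: "A p<0.05 will be taken as threshold of statistical significance". No separate level is given for the preliminary tests.
- Summary: mean with SD "if normally distributed based on Shapiro-Wilk test", otherwise median with quartiles.
- Pre/post comparison of continuous data: "Student’s t-test (continuous data, normally distributed), Mann-Whitney U-test (continuous data, non-normally distributed". No unequal-variance t-test is named, and nothing is said about what follows from Levene's result.
- Strata: NOM versus operative treatment, then, as feasible, examples such as time since implementation, prefracture mobility, ADL status and fracture classification.

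Results "per participating centre and for all participating centres combined" are stated for the NOM rate only. The section on outcome measures adds: "The datasets of all hospitals will be combined for the final analysis".

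**The concern.** A normality test answers whether the sample is large enough to detect a departure from normality. It does not answer which summary or test suits the variable. In a national registry sample, trivial departures are detected; in a small stratum, real skewness often is not. The text also does not say whether normality is judged on the pooled data, per period or per stratum. The same variable could then appear as mean (SD) in one column and median (quartiles) in the next, with different tests behind the p-values, and the two could not be compared.

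Levene's test is a second preliminary test, with no action attached. If the t-test branch is reached, the only version named assumes equal variances. That matters when the SDs differ and the two periods differ in size, which is likely because the baseline is fixed at two years while follow-up after implementation depends on when a hospital starts.

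**Working it through.** **1. Pooled sample size.** The Sample size calculation section gives 17 225 patients aged 70 or older, about 25% of them in institutions: 0.25 × 17 225 = 4,306, which reproduces the stated figure of about 4300. About half meet the criteria: 4,306 / 2 = 2,153, or about 2,150 a year. A two-year baseline is then about 2 × 2,150 = 4,300 patients nationally.

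**2. Shapiro-Wilk rejection rate by sample size.** Simulated at the 0.05 level, with 1,000 samples per cell up to n = 50 and 200 at pooled size. All distributions are assumptions: age normal (86, SD 6.5), cut at 70 and in whole years; length of stay lognormal with log-SD 0.3 (mild skew) or 0.6 (strong skew, whole days); Katz 0–6 beta-binomial; satisfaction 0–10 centred near 8.

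| Variable | n = 15 | n = 30 | n = 50 | n = 2,150 and 4,300 |
|---|---|---|---|---|
| Age | 4% | 5% | 4% | 100% |
| Stay, mild skew | 19% | 37% | 59% | 100% |
| Stay, strong skew | 53% | 87% | 98% | 100% |
| Katz ADL | 23% | 71% | 100% | 100% |
| Satisfaction | 34% | 85% | 100% | 100% |

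Age moves to median and rank test in the pooled table only because n is large. Mildly skewed stay often gets mean and t-test in a small stratum only because n is small.

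**3. Discordance between periods.** Suppose a stratum has 60 baseline and 30 post-implementation patients (assumed) and normality is judged per period. With rejection probabilities p60 and p30, the chance that the two periods get different verdicts is p60(1 − p30) + (1 − p60)p30.

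- Log-SD 0.3: 0.637 × 0.629 + 0.363 × 0.371 = 0.54.
- Log-SD 0.6: 0.997 × 0.137 + 0.003 × 0.863 = 0.14.

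**4. Student's t with unequal variances.** Take period sizes 2n and n and SD ratio 1.5 (both assumed). In large samples the actual two-sided error is P(|Z| > 1.96 × √(V_S / V)), where V_S is the variance Student's test uses and V is the true variance of the difference.

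- Larger SD in the smaller period: pooled variance (2 × 1 + 2.25) / 3 = 1.417; V_S = 1.417 × 1.5 / n = 2.125 / n; V = 1 / (2n) + 2.25 / n = 2.75 / n. Critical value 1.96 × √(2.125 / 2.75) = 1.723, error 8.5%.
- Larger SD in the larger period: V_S = 2.75 / n and V = 2.125 / n. Critical value 1.96 × √(2.75 / 2.125) = 2.230, error 2.6%.

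Simulation (4,000 runs per cell) agrees. At 4,300 v 2,150, Student gave 8.6% and 2.6%, Welch 4.9% and 5.1%. At 60 v 30, Student gave 8.6% and 2.3%, Welch 5.3% and 4.8%. With equal SDs both were about 5%.

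**The case against.** The strongest reply is that little depends on this. The primary outcome is a proportion and goes to a χ² or Fisher's test, so neither preliminary test touches it. If Shapiro-Wilk rejects at pooled size, length of stay, ICU stay and Katz ADL get median, quartiles and Mann-Whitney there, which is a sensible treatment; for age, that treatment is valid too. Student's t would then seldom be reached in the pooled analysis, so its error rate matters mainly in small strata. The size ratio, SD ratio and skewness are all assumed, and no document suggests that SDs differ 1.5-fold between periods. At a 4:3 size ratio with the same SD ratio, the error falls from 8.5% to about 6.4%. All of this stands, and it makes the point minor.

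Three stronger readings are tempting and are not supported:

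- A reader might infer that hospitals will get different summaries and tests from one another. The article states per-centre results for the NOM rate only, does not list hospital among its strata, and pools the data for the final analysis. Audit data as mirror information and quarterly discussion of interview results with centres are mentioned, but without a per-hospital continuous analysis.
- A reader might infer that every pooled variable will be called non-normal. That depends on shape and size: the assumed age distribution was rejected in only about 25% of samples at n = 300, and exactly normal data in about 5% to 9% at pooled size.
- A reader might infer that satisfaction is exposed to the wrong pre/post test. It is collected in phase 3 only, after implementation starts, so it has no baseline score; only its summary is affected.

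It can also be said that an article may leave the choice of t-test version to a fuller plan. That is fair for Levene's missing consequence. It does not cover the Shapiro-Wilk rule, which is written out here, so a fuller plan would have to contradict it.

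**Conclusion.** The point holds as a minor one. The article fixes a data-driven rule under which the summary and test for a continuous variable can differ between the pre and post periods, between planned strata, and between pooled and subset tables. Under the assumed distributions, the rejection rate for mildly skewed stay runs from 19% at n = 15 to 100% at pooled size, and in a stratum of 60 and 30 patients the two periods would disagree in about 14% to 54% of cases, depending on skewness. Levene's test has no stated consequence. Where the t-test branch is used with unequal sizes and SDs, Student's error is wrong in either direction: about 8.5% or 2.6% in the illustration, against about 5% for Welch.

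The distributions, stratum sizes, 2:1 size ratio and SD ratio of 1.5 are assumptions. The direction of the findings does not rest on one exact value, but their size does. No conclusion about the NOM rate changes.

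**What to change.** Delete the Shapiro-Wilk and Levene preliminary tests. Name the summary and test for each continuous variable in advance, from its type and expected shape, and use that choice in every period and stratum and in the pooled table. For example:

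- Age: mean (SD), Welch's t-test.
- Length of stay, ICU stay and Katz ADL: median (quartiles), Mann-Whitney, and a difference between periods with 95% CI (Hodges-Lehmann or bootstrap).
- Satisfaction: median (quartiles), no pre/post test.

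The cost is about two sentences of analysis wording. No extra data are needed, and Welch's test loses essentially nothing when the SDs are equal: both versions were at about 5% in the simulation.
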